### Secondary endpoints

Secondary endpoints include local tumor control, duration of pain response, toxicity, vertebral compression fractures, QOL, and overall survival. Evaluation of local tumor control will be based on imaging acquired during follow-up. Duration of pain response starts at response until pain progression or end of follow-up using information provided by the BPI. A radiation oncologist records toxicity according to the National Cancer Institute’s Common Terminology Criteria for Adverse Events, version 4.0 [21] six weeks after radiation treatment. Toxicity occurring after 6 weeks, (serious) adverse events (SAEs), and hospitalization are registered in the context of the PRESENT cohort. Information about toxicity is based on clinical follow-up data and biannual patient-administered questionnaires on health status and hospitalization. All patients in the SBRT arm undergo an additional MRI scan six months after radiation in order to assess vertebral compression fractures. Since most compression fractures occur four months after radiation treatment [22], this 6-month-MRI captures most incidents. In case of clinical suspicion of a vertebral compression fracture, obtaining the MRI scan will be advanced as deemed appropriate. Quality of life is measured by the EORTC QLQ-C15-PAL general questionnaire [23] and the bone metastases-specific module, the EORTC QLQ-BM22 [24]. The EORTC QLQ-C15-PAL is an abbreviated 15-item version of the EORTC QLQ-C30 specially developed for use in palliative care. In order to evaluate the cost-effectiveness, patients are also provided with the EQ-5D questionnaire. Patients fill out these QOL questionnaires and the BPI before the start of radiation treatment (baseline) and after one, two, three, and six months, and every six months thereafter. The BPI is provided after two and six weeks as well. We make use of the digital patient tracking system PROFILES, so patients are able to complete the questionnaires online after secured login [25]. Overall survival is monitored within the PRESENT cohort by clinical follow-up and via an electronic link with the Municipal Personal Records Database.

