## Methods/design

### Study design

This study is conducted within the Prospective Evaluation of interventional StudiEs on boNe meTastases (PRESENT) cohort [12]. All patients with bone metastases referred to the departments or radiation oncology or orthopedic surgery of the University Medical Center Utrecht are asked to participate in this prospective, observational cohort. Baseline and follow-up data are collected from clinical files, and patient-reported outcomes (PROMs, i.e. a pain inventory and QOL questionnaires) are collected at fixed time intervals. This study follows the cohort multiple randomized controlled trial (cmRCT) design as described by Relton and colleagues [13].

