### Random selection

Eligible patients are randomly selected from the sub cohort on a 1:1 basis with varying block sizes (*n* = six or eight) using an in-house randomization computer program. The radiation oncologist will offer the experimental intervention (i.e. SBRT) to the randomly selected patients. If they accept the treatment offer, they will sign informed consent for participation in the VERTICAL study. Patients who refuse the SBRT will receive care as usual (i.e. standard radiotherapy). According to the cmRCT design, patients in the sub cohort who are not randomly selected will not be informed about the experimental intervention, nor will they be informed about their participation in the control arm of the VERTICAL study. Outcomes in randomly selected patients are compared with the outcomes in eligible patients not randomly selected who received standard radiotherapy (Fig. 1).

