### Data analysis

Data will be analyzed according to the intention to treat principle. Data of eligible patients who were randomly offered stereotactic radiotherapy will be compared with eligible patients who were not randomly selected and received standard radiotherapy. In case of dropout (i.e. patients not surviving longer than three months or patients unable to provide pain scores and analgesic use), a worst-case analysis will be performed: dropped-out patients will be classified as non-responders. In case of substantial refusal of the SBRT offer in the intervention arm, instrumental variable analysis will be used to account for non-compliance [26]. The primary outcome (i.e. proportion of patients with response to radiotherapy) will be presented in absolute numbers and proportions. Differences in pain response will be compared by χ2 test. If randomization fails, imbalances between baseline characteristics will be adjusted by logistic regression analysis. Differences in duration of response and overall survival will be analysed by Kaplan-Meier analysis and log rank test. Toxicity will be presented as the overall incidence of grade 3–4 toxicity and incidence of vertebral compression fractures. Differences will be tested with the χ2 test. A comparison in QOL will be made between the baseline QOL and at predefined intervals after treatment. A change of 10% of the scale breadth will be considered a clinically relevant change of QOL [27]. Data will be presented as improved (≥10% increase), stable, or worsened (≥10% decrease) QOL. We will evaluate the pattern of QOL as a continuous outcome over time using mixed models. Differences with a *P*-value <0.05 will be considered statistically significant. We have planned to perform an interim analysis after inclusion of half of the patients (i.e. 55 patients) when they have completed their follow up (i.e. three months pain assessment).

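### Local tumor control is scored on whatever follow-up imaging exists, but the only scheduled follow-up scan is in the SBRT arm, so an arm comparison would rest on unequal ascertainment

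*Protocol article*

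**What the plan says.** All references are to the protocol article, Methods/design.

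- Secondary endpoints, list: "Secondary endpoints include local tumor control, duration of pain response, toxicity, vertebral compression fractures, QOL, and overall survival".
- Secondary endpoints, source of the local control assessment: "Evaluation of local tumor control will be based on imaging acquired during follow-up". No modality, time point or arm is attached to this sentence.
- Secondary endpoints, scheduled imaging: "All patients in the SBRT arm undergo an additional MRI scan six months after radiation in order to assess vertebral compression fractures". The same section allows this scan to be brought forward: "In case of clinical suspicion of a vertebral compression fracture, obtaining the MRI scan will be advanced as deemed appropriate". No follow-up scan is scheduled for control patients.
- Random selection: controls are not told about SBRT, "nor will they be informed about their participation in the control arm of the VERTICAL study". The comparison is then stated in general terms: "Outcomes in randomly selected patients are compared with the outcomes in eligible patients not randomly selected who received standard radiotherapy". The Data analysis section repeats that comparison under intention to treat.
- Study design: "Baseline and follow-up data are collected from clinical files, and patient-reported outcomes". Only the patient-reported outcomes are said to be collected at fixed intervals.
- Data analysis: the worst-case rule for dropout covers "patients not surviving longer than three months or patients unable to provide pain scores and analgesic use". It is written for the pain endpoint and does not reach imaging.

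**The concern.** Local tumor control can be scored only from a scan. The plan guarantees a scan at a fixed time in one arm and leaves the other to whatever usual care produces. Describing the MRI as additional implies that it comes on top of routine imaging, so the asymmetry is built in.

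Two simple ways of handling unscanned patients then pull in different directions. If they count as controlled, silent progression is found by the scheduled MRI in the SBRT arm and missed among controls, so standard radiotherapy looks better. If they are left out, and usual-care scans are mostly ordered because of symptoms, the scanned controls are a selected group with more progression, so SBRT looks better. A reported difference in local control could therefore reflect scanning practice rather than treatment. An analysis plan written later cannot repair this: it can choose between counting rules but cannot supply the missing control scans.

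**Working it through.** The article gives no sample size, progression rate or imaging rate for local tumor control, so there is no figure of its own to reproduce. The check asks how far two arms with identical true progression would appear to differ.

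**Inputs**
- n = 55 per arm (Sample size considerations).
- L = true local progression, the same in both arms. Assumed 20%, range 10% to 30%.
- m = share of the SBRT arm that has the six-month MRI. Assumed 0.73. This follows the article's 90% acceptance and 10% dropout, with the dropout applied twice to reach six months: 0.90 × 0.90 × 0.90 = 0.729. The article's dropout includes patients who cannot give pain scores but could still be scanned, so 0.73 is an assumption and not a bound.
- a, b = probability of a usual-care scan for patients with and without progression. Assumed 0.40 and 0.15, ranges 0.30 to 0.60 and 0.10 to 0.30. The article gives neither.

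**Rule 1: unscanned patients count as controlled.** Observed progression:
- SBRT: L × [m + (1 − m) × a] = 0.20 × (0.73 + 0.27 × 0.40) = 0.20 × 0.838 = 16.8%
- Control: L × a = 0.20 × 0.40 = 8.0%

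**Rule 2: scanned patients only.** Observed progression:
- SBRT: share scanned = 0.73 + 0.27 × (0.20 × 0.40 + 0.80 × 0.15) = 0.73 + 0.27 × 0.20 = 0.784; progression = 0.168 / 0.784 = 21%
- Control: share scanned = 0.20 × 0.40 + 0.80 × 0.15 = 0.20, which is 11 of 55; progression = 0.08 / 0.20 = 40%

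The truth is 20% in both arms.

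**False-positive rates.** 100,000 simulated trials, 55 per arm, Pearson χ² test at two-sided 5%:

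| Assumptions | Rule 1 | Rule 2 |
|---|---|---|
| L = 20%, a = 40%, b = 15% | about 28%, against SBRT | about 27%, in favour of SBRT |
| L 10–30%, a 30–60%, b 10–30%, all combinations | about 8–60% | about 4–73% |
| L = 20%, a = 80%, b = 70% | about 7% | about 6% |

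The low end of the rule 2 range arises when usual-care scanning is unrelated to progression (30%/30%). The high end arises when it depends on it strongly (60%/10%).

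**Two checks on what drives the result**
- Frequent usual-care scanning (80%/70%). Rule 1: SBRT 0.20 × (0.73 + 0.27 × 0.80) = 18.9%, control 16.0%. Rule 2: control 0.16 / (0.16 + 0.80 × 0.70) = 0.16 / 0.72 = 22%; SBRT 0.189 / (0.73 + 0.27 × 0.72) = 0.189 / 0.924 = 20%. The distortion is small.
- Scanning unrelated to progression (50%/50%). Rule 2 shows 20% in both arms and a false-positive rate of about 5%. Rule 1 is still distorted: SBRT 0.20 × (0.73 + 0.27 × 0.50) = 17.3%, control 10.0%.

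**The case against.** Several counter-arguments are fair, and they limit the point.

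- **No test is named.** The Data analysis section gives methods for pain response, duration of response, survival, toxicity, fractures and quality of life, but none for local tumor control. A reader might infer that a between-arm test of local control is planned; the article does not say so. What it does state is a general comparison of selected with non-selected patients, and nothing exempts this endpoint.
- **The MRI is for fractures.** Its stated purpose is fracture assessment, and local control could be meant to rest on routine imaging in both arms. But the scan is imaging acquired during follow-up, and the text does not exclude it.
- **Scoring detail belongs elsewhere.** The absence of a rule for unscanned patients is something an article may leave to the full protocol or analysis plan, and it is not the fault raised here. The fault is the one-arm schedule, which the article does fix.
- **The usual-care scanning rate is unknown.** A reader might infer that most controls will be unscorable, or that the SBRT arm can have at most about 45 of 55 patients scanned. The article supports neither. It gives no usual-care imaging rate, its dropout figure includes patients who can still be scanned, and the MRI may be brought forward. If usual-care scanning is frequent, the distortion nearly vanishes.
- **The cohort protocol is not shown.** It might schedule imaging for everyone. Nothing in the article says so, and calling the SBRT scan additional points the other way.
- **Limited reach.** The primary pain endpoint and the sample size are untouched. The same one-arm scan also affects fracture detection, so the two issues share a root.

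**Conclusion.** The point stands as one of differential ascertainment of a secondary endpoint. As written, the SBRT arm has a scheduled scan and the control arm does not, so a between-arm comparison of local tumor control would mix treatment effect with scanning practice. If the SBRT arm in the imaging sentence means those actually treated, patients who refuse SBRT lack the scan too, and the intention-to-treat arm is itself unevenly imaged.

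The direction depends on how unscanned patients are counted and on whether usual-care scans follow symptoms. The size cannot be fixed from the article. It ranges from close to the nominal 5% to severe, and every figure above rests on assumed progression and scanning rates. This should be corrected, but it does not threaten the trial's main conclusion.

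**What to change.** State in the protocol or analysis plan that local tumor control will be reported descriptively, by arm. For each arm, give the number scanned (separating scheduled MRI from usual-care imaging), the number who died before any scan and the number not scanned. State also that no between-arm test will be done and no efficacy claim made for this endpoint.

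Keeping a between-arm figure by discarding progressions seen only on the scheduled MRI would not solve the problem. A patient whose progression is found that way may be managed before symptoms would have prompted a scan, so events would be removed from the SBRT arm only.

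The cost is wording only, with no added scans and no change to the design in which controls are unaware of their role. The trial gives up a between-arm claim on local control that its imaging schedule cannot support.

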### Primary endpoint

Primary endpoint of this study is complete or partial pain response at three months. Pain response is defined according to the International Bone Metastases Consensus Endpoints for Clinical Trials (Table 2) [19]. A pain score of zero with no concomitant increase in analgesic intake compared to baseline is defined as complete response. Partial response is pain reduction of at least two points on a scale of 0–10 without increase in analgesic intake and/or analgesic reduction of at least 25% from baseline without an increase in pain. Pain progression is defined as an increase in pain score of at least two points above baseline with stable analgesic use and/or as an increase of at least 25% in analgesic use compared to baseline with at least stable pain scores. All responses not captured with complete and partial response or pain progression are considered indeterminate response. Pain is measured by the Brief Pain Inventory (BPI), which has been validated for use in advanced cancer patients to assess pain and functional interference stemming from bone metastases [20].

**Table 2 Tab2:** Response rate to radiotherapy according to the international consensus [19]

Responders	
Complete response	Pain score of 0 and stable or reduced OMED
Partial response	Pain reduction of 2 points on a 0–10 scale or more and/or OMED reduction by 25% or more
Non-responders	
Pain progression	Increase of 2 points on a 0–10 scale or more above baseline, and/or OMED increased by 25% or more
Indeterminate response	Any response including stable disease that is not captured by complete or partial response or pain progression

*OMED* daily oral morphine equivalent

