### Sample size considerations

Based on the most recent meta-analysis, we expect a pain response in 60% of patients following standard radiotherapy [3]. Pain response after stereotactic radiotherapy is assumed to be 85% [8, 9]. We expect that approximately 90% of patients who are offered SBRT treatment, will accept the offer. Cross-over from control arm to the SBRT treatment arm is extremely unlikely, since only patients who are randomly selected to receive SBRT are informed about the treatment. Taking a one-sided α of 5% and a power of 80%, we require 49 patients per treatment arm to show a statistically significant difference of 15% in pain response. The reason to choose a one sided α is that, although improbable, inferior pain response after stereotactic treatment would lead to the same action as no difference at all between the two treatment regimen. This is because the SBRT treatment will only be implemented if it is significantly better than the usual care, since SBRT treatment is more complex, less convenient for patients, and more expensive than standard radiotherapy. Finally, to allow for a 10% drop out rate, recruitment of 55 patients per group is intended. We expect to complete recruitment within 18 months based on the number of patients we treat in our center annually.

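### Duration of pain response is tested by log-rank among responders only, so the comparison is not protected by randomisation and can be biased in either direction

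*Protocol article*

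**What the plan says.** Under Secondary endpoints, the protocol article sets the clock: "Duration of pain response starts at response until pain progression or end of follow-up using information provided by the BPI". Under Data analysis it sets the test: "Differences in duration of response and overall survival will be analysed by Kaplan-Meier analysis and log rank test", with P below 0.05 counted as significant.

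The same section opens with the general principle: "Data will be analyzed according to the intention to treat principle". For patients who do not survive three months or cannot give pain scores and analgesic use, it adds that "dropped-out patients will be classified as non-responders".

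The event that ends a response is defined under Primary endpoint: "Pain progression is defined as an increase in pain score of at least two points above baseline with stable analgesic use", and/or a rise of at least 25% in analgesic use with pain at least stable. Death is not part of that definition. The article gives no version of the duration analysis that covers all randomised patients, and does not label the comparison as descriptive.

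**The concern.** A log-rank test between randomised arms is normally read as a randomised comparison. This one is not. The clock starts at response, so entry depends on something that happens after random selection and that the trial expects SBRT to make more frequent. The two responder groups can then differ in prognosis for reasons unrelated to how long SBRT makes relief last. The SBRT group contains patients whose counterparts in the control arm did not respond and so were left out.

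The Background gives prolonged pain relief as one reason for escalating the dose, so this endpoint bears on the trial's rationale. A P value from the responder-only test could be read as evidence for or against durability when part of it reflects who was admitted to the comparison.

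A smaller matter is death. With pain progression as the only named event, a patient who dies while in response would most naturally be handled as reaching the end of follow-up. Kaplan-Meier would then describe progression as if such patients could still progress.

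**Working it through.** **Inputs from the protocol article (Sample size considerations).** Control: "we expect a pain response in 60% of patients following standard radiotherapy". SBRT: "Pain response after stereotactic radiotherapy is assumed to be 85" per cent. Acceptance: "We expect that approximately 90% of patients who are offered SBRT treatment, will accept the offer". Required size is 49 per arm, raised to 55 for 10% dropout. The article gives no figure for duration of response or mortality, so every duration and death rate below is an assumption.

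**1. Reproducing the plan's own figure.** The expected response rate in the arm offered SBRT is 0.9 × 0.85 + 0.1 × 0.60 = 0.825. The usual two-proportion formula (pooled variance under the null, no continuity correction) for 60% versus 82.5%, one-sided 5%, 80% power, gives 48.98, so 49 per arm; 49 / 0.9 = 54.4, so 55. This matches the stated sizes, so 60% and 82.5% are the right rates for counting responders by arm.

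**2. Who enters the log-rank test.**

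| Base per arm | Control responders | Responders in arm offered SBRT |
|---|---|---|
| 55 recruited | 55 × 0.60 = 33.0 | 55 × 0.825 = 45.4 |
| 49 evaluable | 49 × 0.60 = 29.4 | 49 × 0.825 = 40.4 |

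These are expected counts derived from the three-month rates, not figures that the article plans for.

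**3. What selection does to the medians.** Assume that everyone who would respond to standard radiotherapy would also respond if offered SBRT, with an exponential duration of median 6 months in both arms. The arm offered SBRT then has a further 82.5 − 60 = 22.5% of patients who respond only because of SBRT. Among its responders the shares are 0.60 / 0.825 = 0.727 and 0.225 / 0.825 = 0.273. With median B for the additional responders, the responder median t solves

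0.727 × 2^(−t/6) + 0.273 × 2^(−t/B) = 0.5.

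| B (months, assumed) | SBRT responder median | Control responder median |
|---|---|---|
| 3 | 4.9 | 6.0 |
| 5 | 5.7 | 6.0 |
| 6 | 6.0 | 6.0 |
| 9 | 6.7 | 6.0 |

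For B = 3, at t = 4.91: 0.412 + 0.088 = 0.500. In every row SBRT has the same effect on duration, namely none, for the patients who would respond either way. The contrast moves only because the additional responders differ.

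**4. What this does to the test.** Simulation with 55 per arm, 4,000 runs per scenario, exponential times, assumed mean survival 12 months and 12 months of follow-up from response; offered-arm response 82.5% or 85%.

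- All responders with mean duration 6 months: hazard ratio about 1.00, no systematic direction.
- Additional SBRT responders with mean 2 to 3 months against 6 to 9 for the rest: hazard ratio 1.20 to 1.36 against SBRT. The log-rank points against SBRT in 73–84% of trials and is significant against it (two-sided 5%) in 8–16%.
- In those same scenarios, mean time in response over all randomised patients within 12 months is 0.4 to 0.6 months longer with SBRT. With equal durations it is about 0.9 months longer.

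**5. Death as censoring, if that is what is done.** With assumed monthly hazards of 0.08 for both progression and death, at 6 months:

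- 1 − Kaplan-Meier = 1 − exp(−0.48) = 38%
- true cumulative incidence of progression = 0.5 × (1 − exp(−0.96)) = 31%

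With assumed mean duration 9 months and mean survival 6 to 12 months, the 12-month figures are 74% against 39–52%.

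**The case against.** Four objections deserve an answer.

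**The direction depends on chosen inputs.** This stands. A reader might infer from the 3-month row that the plan will make SBRT look worse. The article does not support that: it gives no durations, and that row also sets to zero the prolongation that the Background hopes for. If the patients who would respond either way have a median of about 8 months on SBRT instead of 6, the responder median returns to 6.0 even with B = 3. With B = 9, selection flatters SBRT.

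**The handling of death is not stated.** This also stands. A reader might infer that the protocol prescribes censoring at death; it does not say so, and such detail is commonly left to an analysis plan. Nor does the example in step 5 show a biased test. With the same death rate in both arms the curves are inflated alike, and a log-rank test that censors deaths still compares cause-specific hazards. The consequence is an overstated probability of progression.

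**An analysis plan may settle the rest.** This does not remove the main point. The article itself fixes the start, the event and the between-arm test, and following it as written yields a P value for groups selected on outcome.

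**It is one secondary result among several.** True. Response, overall survival and quality of life have their own analyses. This limits the weight of the point but does not make the comparison a randomised one.

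**Conclusion.** The point holds in a limited form. As defined, the log-rank comparison of duration of response admits only responders, about 33 versus 45 of 55 per arm (29 versus 40 of 49 evaluable). It therefore conditions on a post-randomisation outcome that the trial expects to differ by 22.5 percentage points, which does not fit the article's intention-to-treat principle.

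The resulting bias has no fixed sign. Under the assumed durations the SBRT responder median ranges from 4.9 to 6.7 months against 6.0 in control, and there is no distortion if the additional responders last as long as the others. Those figures rest on exponential durations, on no patient losing a response through being offered SBRT, and on no true prolongation. They illustrate the mechanism and do not predict the result.

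Censoring at death is the natural reading but only an implied one; where it is used and deaths occur before progression, 1 − Kaplan-Meier overstates the probability of progression. The primary analysis and the sample size are unaffected. The change should be made, since a formal P value is planned for a question that belongs to the trial's rationale.

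**What to change.** Make the between-arm comparison one of time in response over all randomised patients, by arm as randomly selected. Suitable wording would be:

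*Time in pain response will be measured for every randomised patient from random selection to a prespecified horizon. Non-responders contribute zero. A response ends at pain progression or death, whichever comes first. Mean time in response will be compared between the arms. Among responders, pain progression will be shown as cumulative incidence with death as a competing event. Kaplan-Meier curves restricted to responders will be descriptive, without a P value.*

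The cost is some additional analysis work. The serial Brief Pain Inventory (BPI) data and survival, through the link to the municipal records database, are already collected. No visit, treatment or sample size changes.

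There are two downsides. The summary is less familiar and partly reflects survival as well as pain control, so it should be reported beside overall survival. Timing is also coarse after month 6, when the BPI becomes six-monthly, so the horizon should coincide with a scheduled assessment and the rule for dating progression between visits should be fixed in advance.

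### Only the SBRT arm has a scheduled six-month MRI for vertebral compression fractures, yet fracture incidence is tested between arms, so unequal detection alone can produce an apparent SBRT excess

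*Protocol article*

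**What the plan says.** In the protocol article, Secondary endpoints lists vertebral compression fractures among six secondary endpoints. On how they are found, it says: "All patients in the SBRT arm undergo an additional MRI scan six months after radiation in order to assess vertebral compression fractures". It expects that "this 6-month-MRI captures most incidents", and adds: "In case of clinical suspicion of a vertebral compression fracture, obtaining the MRI scan will be advanced as deemed appropriate".

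No control-arm scan is described. The only late route given for controls is the cohort's: "Information about toxicity is based on clinical follow-up data and biannual patient-administered questionnaires on health status and hospitalization". Under Random selection, controls are not told of the experimental treatment, "nor will they be informed about their participation in the control arm of the VERTICAL study".

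Data analysis sets an intention-to-treat comparison of patients offered SBRT with those not selected. It then says: "Toxicity will be presented as the overall incidence of grade 3–4 toxicity and incidence of vertebral compression fractures". The next sentence applies the chi-square test to differences, and P below 0.05 counts as significant. Nothing limits the fracture test to clinically detected fractures or makes the scheduled-MRI findings descriptive.

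For local tumor control, Secondary endpoints says only: "Evaluation of local tumor control will be based on imaging acquired during follow-up". Data analysis names no test for it.

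**The concern.** In the SBRT arm, fractures with and without symptoms are counted, because the scan is scheduled for everyone. In the control arm, a fracture is counted only if something in routine care brings it to light. The chi-square test cannot separate a difference in fracture risk from a difference in how hard each arm was searched. If the true risks are equal, the expected result is still more recorded fractures with SBRT. The plan would report that as a toxicity difference with a P-value, and it would weigh on how the treatment is judged.

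This is not detail that an article leaves to a fuller document: the article itself states both the one-arm scan and the between-arm test. That only the SBRT arm is scanned is an inference, but a firm one. The scan is called additional, is assigned to that arm, and has no counterpart elsewhere in the text.

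**Working it through.** **Inputs from the article.** Arm size is 55 (Sample size considerations). It reproduces from the 49 evaluable per arm with 10% dropout: 49 / 0.9 = 54.4, rounded up to 55. The threshold is P < 0.05, taken here as two-sided, so the nominal chance of a false excess in the SBRT direction is 2.5%. Expected acceptance of SBRT is about 90%. The article states no fracture rate and no power for this endpoint, so there is no planned figure to reproduce.

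**Assumptions.** True fracture risk p is the same in both arms, 5% to 20%. Control follow-up finds a share s of what the scheduled MRI would find: 1, 3/4, 1/2 or 1/3.

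**Method.** With everyone in the SBRT arm scanned, the recorded risks are p (SBRT) and s·p (control). For x and y recorded fractures and n = 55 per arm,

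z = (x/n − y/n) / √(2·q(1 − q)/n), with q = (x + y)/(2n).

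The chance of a false SBRT excess is the sum of Bin(x; n, p) × Bin(y; n, s·p) over all (x, y) with z > 1.96. This is exact enumeration of the uncorrected chi-square test.

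Example: p = 10% and s = 1/2 give recorded risks of 10% and 5%, or 5.5 and 2.75 expected fractures, with a recorded risk ratio of 2.0. The chance of a false excess is 16%.

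| True risk, both arms | s = 1 | s = 3/4 | s = 1/2 | s = 1/3 |
|---|---|---|---|---|
| 5% | 2.2% | 4% | 8% | 13% |
| 10% | 2.5% | 7% | 16% | 27% |
| 15% | 2.5% | 8% | 23% | 42% |
| 20% | 2.6% | 10% | 31% | 55% |

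**If part of the SBRT arm is not scanned.** Let a fraction f be scanned and the rest be detected as controls are. The recorded SBRT risk becomes f·p + (1 − f)·s·p.

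- f = 0.9 (refusers not scanned), s = 1/2: 7%, 14%, 20% and 27% at true risks of 5%, 10%, 15% and 20%.
- f = 0.7, p = 15%, s = 1/2: 0.105 + 0.0225 = 12.75% against 7.5%, giving 14%.
- f = 0.5, same p and s: 0.075 + 0.0375 = 11.25% against 7.5%, giving 10%.

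**If only 35 per arm are evaluable at six months (assumption).** With s = 1/2 and all scanned: 4%, 12%, 18% and 22% at the same four risks.

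Only the s = 1 column sits at the nominal level. The direction follows from the schedule; the size follows from the assumptions.

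**The case against.** The strongest reply is that the effect may be modest and that it runs against SBRT. The article does not show how many fractures are missed in controls, and full scanning of 55 patients is the extreme case. About 10% are expected to refuse, the life-expectancy exclusion covers only those under three months, and since the 2015 amendment some patients have non-spinal lesions only. It is also unclear whether the SBRT arm, for scanning, means all who were offered SBRT or only those who accepted. This stands as a limit on size, and the partial-scanning figures reflect it. It does not remove the problem. Detection bias works against SBRT, so a result showing no excess would be conservative in that respect, but a result showing an excess could not be interpreted.

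A second objection concerns the remedy. Dropping fractures first seen on the scheduled MRI, with no time limit, would also drop SBRT-arm fractures that would later have caused symptoms, while the same fractures in controls would be counted. That is correct, and the comparison must therefore stop at the six-month scan. The trial is also open-label, and SBRT patients have a scan that can be brought forward, so the threshold for imaging may still differ between arms. That residue cannot be removed by analysis.

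Some stronger readings are not supported:

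- A reader might infer that the test hides a fracture reduction with SBRT. The stereotactic radiotherapy section mentions a potential advantage of the boost technique, from sparing healthy bone, but no passage expects fewer fractures than with standard radiotherapy.
- A reader might see patients with only non-spinal lesions as a further bias. They enter both arms by random selection, so they dilute incidence without favouring either arm.
- A reader might conclude that the local-control comparison is equally flawed. The article states no such test, so this is only a caution.

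**Conclusion.** The point holds for the fracture endpoint. As written, the plan compares an arm screened by MRI with an arm followed clinically, and no other section repairs this. With 55 per arm, equal true risk of 5–20% and full scanning, the chance of a falsely significant SBRT excess is 4–10%, 8–31% or 13–55% when control follow-up finds three quarters, half or one third of fractures. Incomplete scanning lowers these figures. All rest on assumed fracture and detection rates.

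This is a change that should be made, not one on which the trial's validity turns. A reader might treat fracture as the trial's key safety outcome and rate the point higher, but the article lists it as one of six secondary endpoints. The primary endpoint is untouched, and Sample size considerations frames adoption of SBRT around superiority over usual care in a calculation based on pain response. What is at risk is an apparent excess of harm, not a change in true risk.

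**What to change.** Before analysis, amend the toxicity paragraph of Data analysis as follows:

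- Restrict the between-arm fracture test to fractures found after clinical suspicion, in both arms, from radiation up to the six-month scan (the same time point in controls). Exclude those first seen on the scheduled MRI.
- Use patients with a spinal index lesion as the denominator. This removes dilution, not bias.
- Report fractures first seen on the scheduled MRI descriptively, for the SBRT arm only.
- Record what triggered each scan, so that a scan brought forward on suspicion can be told from a scheduled one.
- If local tumor control is compared between arms, leave the protocol-only MRI out of that comparison too.

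The cost is a wording change and one data field. No extra scans are needed, and controls remain unaware as the cohort design requires. The price is fewer events: at 10% true risk and half detection, about 55 × 0.05 = 2.75 expected fractures per arm, so the test will say little and the estimate with its interval will matter more. If the threshold for imaging is the same in both arms, the chance of a false excess returns to about the nominal level. Any open-label difference in that threshold remains and should be stated as a limitation.
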